## Abstract

**Background:**

What study participants think about the nature of a study has been hypothesised to affect subsequent behaviour and to potentially bias study findings. In this trial we examine the impact of awareness of study design and allocation on participant drinking behaviour.

**Methods/Design:**

A three-arm parallel group randomised controlled trial design will be used. All recruitment, screening, randomisation, and follow-up will be conducted on-line among university students. Participants who indicate a hazardous level of alcohol consumption will be randomly assigned to one of three groups. Group A will be informed their drinking will be assessed at baseline and again in one month (as in a cohort study design). Group B will be told the study is an intervention trial and they are in the control group. Group C will be told the study is an intervention trial and they are in the intervention group. All will receive exactly the same brief educational material to read. After one month, alcohol intake for the past 4 weeks will be assessed.

**Discussion:**

The experimental manipulations address subtle and previously unexplored ways in which participant behaviour may be unwittingly influenced by standard practice in trials. Given the necessity of relying on self-reported outcome, it will not be possible to distinguish true behaviour change from reporting artefact. This does not matter in the present study, as any effects of awareness of study design or allocation involve bias that is not well understood. There has been little research on awareness effects, and our outcomes will provide an indication of the possible value of further studies of this type and inform hypothesis generation.

**Trial Registration:**

Australia and New Zealand Clinical Trials Register (ANZCTR): ACTRN12610000846022

## Background

The "Hawthorne effect", also known as *reactivity*, refers to the possibility that people may change their behaviour simply because they know they are participating in a study [1]. The name derives from studies done in the workplace at the Western Electric Plant in Hawthorne, Illinois from 1924-32. It is well accepted that there is unintended reactivity by participants in randomised controlled trials [2-4]. Placebo control conditions have been developed in pharmacological trials and elsewhere to control for the effects of disappointment at allocation outcome as well as for the placebo effect itself [5,6]. Despite longstanding awareness of reactivity [1], we are aware of only one experimental study measuring the size of the aggregate effect. This study found the effect to be large: approximately 1.5 standard deviations maintained for six months on an objectively ascertained outcome without scope for information bias [7]. However, this dental experiment compared one group, led to believe both that they were in a trial and in receipt of experimental toothpaste, with a second group from whom consent was not obtained and who were unaware of research participation. This design means that the specific effects of trial participation cannot be separated from the broader effects of research participation. There are also many possible explanations for the observed differences including research recruitment, research assessment, randomisation and placebo effects. Of these, assessment reactivity or mere measurement effects have attracted considerable recent attention [8-11] and there is an extensive and advanced literature on placebo effects [6,12,13].

In addition to possible effects in the recruitment phase of a randomised controlled trial (RCT), the process of randomisation itself may be perceived by participants as odd or confusing [2,14]. This uncertainty about how participants view the process of taking part in RCTs leads logically to the question of whether participation in these studies generates sufficient reflection upon behaviour to impact upon the outcomes of interest. An experimental contrast with participation in a non-randomised study is needed to evaluate this possibility.

This study, funded via a project grant from the Australian Research Council, will examine the effects of participants' knowledge of research design, comparing the effects of participation in a cohort study, with participation in a RCT. The behavioural focus of the study will be alcohol consumption. Participant awareness of study design and random allocation will be experimentally manipulated. Two hypotheses will be tested: (1) that knowledge of participation in a randomised study in comparison to a cohort (i.e., a non-experimental) study alone will reduce participants' alcohol consumption; and (2) that knowledge of allocation to an intervention condition in comparison to a control condition in a randomised trial will reduce participants' alcohol consumption. This latter hypothesis investigates whether placebo effects are influenced by expectancies generated as a result of the trial process rather than solely deriving from the perceived properties of the intervention.

## Methods

### Design

The study design is a multi-centre three-arm parallel group randomised controlled trial (Figure 1). Ethical approval to conduct the study was granted by the University of Otago Ethics Committee (Protocol number: 10/148).

**Figure 1 F1:**
[figure not shown]
**Study design**.

### Setting

The setting is large public universities in New Zealand and Australia and recruitment and randomisation will be undertaken in waves, one university at a time, with adjustment to sample size estimates after preliminary analyses at each stage. This design is not to be confused with the stepped wedge design, as participants are randomised to the three experimental conditions as they are recruited.

### Procedure

All students will be invited by e-mail to participate in an on-line "Research project on student drinking". Students will be informed that "The study involves the completion of two short web surveys each one month apart" and asked to click on a hyperlink which takes them to the study website (URL) and information form (http://www.behaviourscience.net/InformedConsent.pdf). Clicking on a link to complete the first survey will be taken as consent. A reminder message will be sent two weeks later.

### Screening

The baseline survey will be comprised of questions about alcohol intake and other behaviour (available at http://behaviourscience.net/). Any participant whose answers indicate a moderate to high level of alcohol intake (indicated by a score of 4 or more on the AUDIT-C [15]) will be randomised to one of three conditions. Those who score less than 4 on the AUDIT-C will be thanked for participating and provided with a link to *Alcohol: The Basics*, a page containing information about effects of alcohol, safe drinking levels and problems associated with drinking, such as drink-driving (Figure 2).

**Figure 2 F2:**
[figure not shown]
***Alcohol: The Basics *material**.

### Randomisation

Following screening, participants will be randomised without their knowledge to one of three conditions (A-C). Randomisation will be effected by computer using a random number generator. Participants will not be informed that they are participating in a randomised study and given the computerised randomisation, the research team will not know which group each participant is assigned to until after outcomes are assessed. There is thus no opportunity for randomisation to be subverted.

### Interventions

Participants in the three experimental groups will also be presented with the opportunity to access the *Alcohol: The Basics *material via a hyperlink. This material was selected *not *to be effective in promoting behaviour change, and there will be identical levels of encouragement to actually read the alcohol health information in each condition. The differences between groups exist solely in the way the study is described to participants (see Figure 1), namely, in what students are told is the design of the study (cohort or trial), along with their allocation status if randomised to the trial. It should be noted that Figure 1 includes the exact text presented to participants with the differences between conditions B and C emboldened here.

### Outcome measurement

At baseline each participant will be advised they will be sent another survey by email in a month's time. The second survey (which can be viewed at http://behaviourscience.net/) contains eight questions about drinking patterns over the past month and participants' impressions of the study. The primary outcome measures will be the frequency, quantity of alcohol consumption per typical drinking occasion (in standard drinks; 10 g ethanol), volume of alcohol consumed in the preceding four weeks and the incidence of hangover in the same period.

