### Sample size estimation

There is no previous research on which to base an expected effect size for this study. Assuming power of 0.80, alpha 0.05, dispersion of 0.2, and a 2-sided test, we would need to analyse 1,946 cases per group at 1 month (i.e., a total N of 5838) we could detect a group difference of 5.5% for comparisons of B v C (Hypothesis 2). This sample size provides additional power to detect an effect of similar size for A v B and C (Hypothesis 1). If the dispersion is greater than anticipated at 0.4, with 5,838 participants at follow-up we will still be able to detect a 7% difference. Accordingly, we will invite all students at the University of Otago (approximately 20,000 individuals), with the expectation of recruiting approximately a third of the total required, which is feasible considering a recent survey at that university [16]. We will then conduct preliminary analyses to estimate an effect size and determine the number to be invited from a second university, and whether a third university is needed.

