### Analysis

Groups B and C will be combined for comparison with group A for testing of Hypothesis 1. Groups B and C will be compared to test Hypothesis 2. Alcohol consumption will be analysed using negative binomial regression, with baseline AUDIT-C score as a covariate to account for regression to the mean. Hangover incidence and other dichotomous variables will be analysed with logistic regression. Results will be presented as risk ratios and odds ratios. Participants will be analysed in the group to which they were randomised (intention to treat). Analyses will be stratified by centre to account for the multicentre nature of the trial.

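### Four unranked primary outcomes are paired with a sample size built on one two-sided 0.05 test, so either the false-positive rate per hypothesis exceeds 0.05 or the stated 80% power for B v C is lost

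*Protocol article*

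**What the plan says.** - **Outcomes.** The Outcome measurement section of the protocol article reads "The primary outcome measures will be the frequency, quantity of alcohol consumption per typical drinking occasion", and the list continues with "volume of alcohol consumed in the preceding four weeks and the incidence of hangover in the same period". That makes four primary outcomes, with no order of importance among them.
- **Hypotheses.** The Background says "Two hypotheses will be tested": one on knowing that the study is randomised, one on knowing the allocation. Both predict a reduction in alcohol consumption, and neither says which measure decides the matter.
- **Contrasts.** The Analysis section says "Groups B and C will be combined for comparison with group A for testing of Hypothesis 1" and "Groups B and C will be compared to test Hypothesis 2".
- **Sample size.** The Sample size estimation section begins from "Assuming power of 0.80, alpha 0.05, dispersion of 0.2, and a 2-sided test", says "we would need to analyse 1,946 cases per group at 1 month (i.e., a total N of 5838"), and states that with this number "we could detect a group difference of 5.5% for comparisons of B v C (Hypothesis 2"). For Hypothesis 1 it claims extra power at the same N and gives no separate significance level.
- **Purpose.** The Discussion part of the Abstract says the results will indicate whether further studies are worthwhile and will help to generate hypotheses.

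The article gives no decision rule for combining the four outcomes. It also makes no claim about an overall error rate.

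**The concern.** Four outcomes and two contrasts give eight primary tests, while the design calculation covers one. The two parts of the text cannot both hold in full. If each outcome is tested at the only level given, the chance that some primary outcome differs by luck is well above 0.05 for each hypothesis. If an adjustment is added later, the planned number no longer gives 80% power for B v C.

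The study asks whether small awareness effects exist at all, and has no earlier effect size to lean on. The Public health relevance section expects the findings to improve the interpretation of existing trials. One significant outcome out of four, with the other three null, would be hard to read, because the text does not say which outcome carries the hypothesis.

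**Working it through.** **Inputs from the protocol article.** Four primary outcomes (Outcome measurement); two contrasts, A v B+C and B v C (Analysis); two-sided alpha 0.05, power 0.80, dispersion 0.2, 1,946 per group, 5.5% difference for B v C (Sample size estimation).

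**Assumptions, not in the article.** The control mean; the correlation ρ between the four test statistics, taken as equal for all pairs; and testing of every outcome at 0.05.

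**Step 1: the plan's own figure.** 3 × 1,946 = 5,838, as stated. For a negative binomial comparison, n per group = (z₀.₉₇₅ + z₀.₈₀)² × (2/μ + 2k) / ln(RR)², with k the dispersion. The mean μ is not given, so 1,946 cannot be derived from the stated inputs alone. Solving for it with RR = 1.055 and k = 0.2 gives μ ≈ 6.44. At μ = 6.2 the formula gives 1,979 for 5.5% at dispersion 0.2, and 1,925 for 7% at dispersion 0.4. Both are within 3% of 1,946. The planned N is therefore consistent with one unadjusted two-sided 0.05 test.

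**Step 2: false positives per hypothesis, no true effect.** With four independent tests the chance of at least one is 1 − 0.95⁴ = 18.5%. Correlated cases come from simulating four equicorrelated normal statistics. If only a significant reduction counts, each test has a 0.025 chance; under independence that gives 1 − 0.975⁴ = 9.6%.

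**Step 3: both hypotheses.** With equal arms the contrast weights (−1, ½, ½) and (0, −1, 1) have product sum 0 − ½ + ½ = 0. The two contrasts are uncorrelated, so the combined chance is 1 − (1 − p)².

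| Assumed ρ | One hypothesis, either direction | Both hypotheses, either direction |
|---|---|---|
| 0 | 18.5% | 33.7% |
| 0.5 | 15.6% | 28.7% |
| 0.7 | 13.0% | 24.3% |
| 0.9 | 9.4% | 17.9% |
| 1 | 5% | 9.75% |

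Counting reductions only, one hypothesis gives 9.6% at ρ = 0 and 6.5% at ρ = 0.7. Over both hypotheses these become 18.3% and 12.6%.

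Equal correlation is a simplification, because volume is built from frequency and quantity. Treating log volume as log frequency plus log quantity (assumed frequency–quantity correlation 0 to 0.4, hangover correlation 0.3 to 0.5) gives 25% to 28% over both hypotheses, either direction.

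**Step 4: power if the four outcomes are adjusted within a hypothesis.** The strictest Holm step, the same as Bonferroni, is 0.05/4 = 0.0125, with critical value 2.498 in place of 1.960.

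- B v C: 80% power at 0.05 implies a standardised effect of 1.960 + 0.842 = 2.802. At 0.0125 power is Φ(2.802 − 2.498) = Φ(0.304) ≈ 62%.
- A v B+C, same effect size: the variance factor falls from 2/1,946 to 1/1,946 + 1/3,892 = 1.5/1,946. The standardised effect is 2.802 × √(2/1.5) = 3.235. Power is Φ(3.235 − 1.960) ≈ 90% at 0.05 and Φ(3.235 − 2.498) ≈ 77% at 0.0125.
- Keeping 80% for B v C at 0.0125 would need 1,946 × ((2.498 + 0.842)/2.802)² ≈ 2,765 per group.

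**The case against.** The strongest reply is that much of the alarm depends on rules the article does not state. Alpha appears once, in the sample size paragraph. The text does not say that each outcome is tested at 0.05, that one significant outcome is enough to support a hypothesis, or that the overall error rate is 5%. A multiplicity rule is commonly left to an analysis plan, which is not shown here, so its absence is not a fault in itself. All of this stands. What it does not answer is that the article itself makes four outcomes primary and sizes the trial on one test. An adjustment placed elsewhere would leave the stated B v C power wrong.

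A reader might go further and infer a false-positive chance of 24% to 34% where 5% was promised. The documents do not support that. No 5% overall rate is promised. The 24% is the result at an assumed correlation of 0.7 and is not a lower limit; the article gives no correlation. Pooling eight tests treats two distinct, prespecified hypotheses as one family, and handling each separately is defensible. Both hypotheses are directional, so false support for them is about half as likely as the two-sided figures suggest.

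A reader might also take 5.5% as the expected effect. The article says no earlier research gives one; 5.5% is the detectable difference.

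Finally, the hypothesis-generating aim softens the consequence, and it would be too strong to say that confirmatory value is lost. It does not remove the problem, because the hypotheses are to be tested, the outcomes are labelled primary and a formal power calculation is given.

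**Conclusion.** The point holds in this limited form and should be fixed, though it does not invalidate the trial. On the inferred reading that each outcome is tested at 0.05, the chance of at least one false-positive primary result per hypothesis is about 13% to 18.5% in either direction, or about 6.5% to 10% for reductions alone, for assumed correlations from 0.7 down to 0. Taken over both hypotheses, the two-sided figure lies somewhere between 9.75% (perfect correlation) and 33.7% (independence), and the documents cannot narrow it.

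On the other reading, with adjustment within a hypothesis, power at the strictest step is about 62% for B v C and about 77% for A v B+C. The stated 80% for B v C therefore holds only for a single unadjusted outcome.

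**What to change.** Before outcome data are analysed, name one primary outcome for both hypotheses in Outcome measurement and make the other three secondary. Four-week volume is a natural candidate, since it reflects both frequency and quantity. State in Analysis that each hypothesis is judged on that outcome at two-sided 0.05. This keeps N, the data collected, and the stated alpha and power for each hypothesis. If the two hypotheses are regarded as one family, the chance of any false positive over both is up to 1 − 0.95² = 9.75%, and the text should say which view is taken. The cost is a sentence or two, and less weight for three outcomes.

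Alternatively, keep all four as primary, apply Holm within each hypothesis, and restate the power in Sample size estimation. The cost is then lower stated power for B v C, or a larger sample (about 2,765 per group to hold 80% at the strictest step).

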### Sample size estimation

There is no previous research on which to base an expected effect size for this study. Assuming power of 0.80, alpha 0.05, dispersion of 0.2, and a 2-sided test, we would need to analyse 1,946 cases per group at 1 month (i.e., a total N of 5838) we could detect a group difference of 5.5% for comparisons of B v C (Hypothesis 2). This sample size provides additional power to detect an effect of similar size for A v B and C (Hypothesis 1). If the dispersion is greater than anticipated at 0.4, with 5,838 participants at follow-up we will still be able to detect a 7% difference. Accordingly, we will invite all students at the University of Otago (approximately 20,000 individuals), with the expectation of recruiting approximately a third of the total required, which is feasible considering a recent survey at that university [16]. We will then conduct preliminary analyses to estimate an effect size and determine the number to be invited from a second university, and whether a third university is needed.

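### Later waves are sized from the between-group effect seen in earlier waves, with no stated alpha adjustment: type I error rises modestly and the resizing rests on a very imprecise estimate

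*Protocol article*

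**What the plan says.** The Setting section describes recruitment in waves, one university after another, "with adjustment to sample size estimates after preliminary analyses at each stage".

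The Sample size estimation section starts from a fixed-sample calculation. The planning values are "Assuming power of 0.80, alpha 0.05, dispersion of 0.2, and a 2-sided test", and the result is that "we would need to analyse 1,946 cases per group at 1 month (i.e., a total N of 5838"), with which "we could detect a group difference of 5.5% for comparisons of B v C (Hypothesis 2"). The first university is expected to yield roughly a third of that total. The section continues: "We will then conduct preliminary analyses to estimate an effect size and determine the number to be invited from a second university", and the same sentence leaves open whether a third university will be used.

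The Analysis section names negative binomial and logistic regressions, stratified by centre. It mentions no method for a data-dependent sample size.

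**The concern.** In this section, effect size means the difference between groups. It opens with "There is no previous research on which to base an expected effect size for this study", and the preliminary analysis is there to fill that gap. A B v C or A v B+C difference cannot be computed without group labels, so the resizing is not arm-blind.

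The first university counts towards the required total, so its data are apparently pooled with the later waves. When the later sample size depends on the effect already observed, the pooled statistic no longer has its nominal distribution. A chance difference in wave 1 leads to a small wave 2, which dilutes it little. A wave 1 result near zero leads to a large wave 2, which gives the test another chance. The result is a type I error above 0.05 and, when a true effect exists, an estimate that is on average too large. Centre coincides with wave, but stratifying by centre does not correct this, because the wave sizes themselves depend on the effect.

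The trial looks for a small difference and exists to measure bias in trials, so even modest exaggeration of its own estimate matters.

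**Working it through.** **Inputs.** From Sample size estimation: alpha 0.05 two-sided, power 0.80, dispersion k = 0.2, 1,946 per group, difference 5.5%, wave 1 about a third of the total. Assumed: the mean count μ, and the resizing rule with its limits, none of which is stated.

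**1. The plan's own figure.** With (1.960 + 0.842)² = 7.849, the negative binomial formula is

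n per group = 7.849 × [(1/μ + k) + (1/(μ·RR) + k)] / ln(RR)².

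Because μ is not stated, 1,946 cannot be derived from the stated inputs alone. Assuming μ = 6:
- RR 1.055, k = 0.2 gives 1,984.
- RR 1.07, k = 0.4 (the protocol's second scenario) gives 1,925.

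Both are within 3% of 1,946, and 3 × 1,946 = 5,838. The fixed-sample figure is therefore plausible, with the difference read as a ratio above 1.

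**2. Precision after wave 1** (1,946 / 3 ≈ 649 per group).
- Without assuming a mean: if 1,946 per group gives 80% power at RR 1.055, the final SE of ln(RR) is 0.0535 / 2.802 = 0.0191. The wave 1 SE is 0.0191 × √3 = 0.0331.
- With μ = 6: √[2 × (1/6 + 0.2) / 649] = 0.0336.
- 95% half-width: 1.96 × 0.0331 = 0.065 to 1.96 × 0.0336 = 0.066 on the log scale, about 6.6%. The target is ln(1.055) = 0.0535.

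If the true difference is 5.5%, the expected wave 1 z is 2.802 / √3 = 1.62, power at that point is 37%, and there is a 5% chance that the estimate has the wrong sign. Re-solving for 80% power at the 10th, 25th, 50th, 75th and 90th percentiles of the wave 1 estimate gives about 45,100, 5,700, 1,946, 970 and 610 per group.

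**3. Type I error and bias.** Let t = 1/3 be the wave 1 share of planned N, and r the later share. Resizing to 80% power at the observed effect sets r = 7.849·t/Z₁² − t, held between a lower and an upper limit. The unadjusted pooled statistic is Z = (√t·Z₁ + √r·Z₂)/√(t + r), tested against 1.96. Simulation of 4 million trials gives:

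| Limits on later waves (share of planned N) | Cap on total | Type I error | Mean estimate of a true 5.5% reduction |
|---|---|---|---|
| fixed at 2/3 (no resizing) | plan | 5.0% | – |
| 1/3 to 2/3 | plan | 5.6% | 5.7% |
| 1/3 to 4/3 | 5/3 of plan | 6.2% | 5.9% |
| 1/3 to 8/3 | 3 × plan | 6.7% | 6.0% |
| 0 to 2/3 | plan | 6.5% | 6.2% |
| 0 to 5/3 | 2 × plan | 7.2% | 6.4% |
| 0 to 8/3 | 3 × plan | 7.5% | 6.4% to 6.5% |

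The upper resized block is closest to the text, which treats the second university as certain and only the third as optional. The lower block lets recruitment end after the first university.

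Other rules give similar results. Sizing on 80% conditional power gives 5.7% (limits 1/3 to 2/3) and 6.3% (1/3 to 4/3). The worst possible rule within those limits gives 5.8% and 6.5%.

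**4. Check of a correction.** With limits 1/3 to 4/3, the unadjusted pooled test has type I error 6.2%. An inverse-normal combination of the two stages, with weights fixed in advance at √(1/3) and √(2/3), has 5.0%.

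**The case against.** The article condenses a fuller protocol, and the analysis plan is not shown. Caps, formulas and an alpha adjustment could sit there, and 0.05 is stated only as a planning value. Some prespecified rules, such as enlarging the trial only when conditional power is already high, would not inflate the error. This stands as a limit on certainty about the size of the problem. It does not remove the point, because the document itself commits to resizing on the effect and pairs that with a single plain alpha and ordinary regressions.

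The team also has a reason to look: nothing earlier informs the effect size, and the protocol does not justify 5.5% as the smallest difference of interest. That reason is fair, but wave 1 cannot supply the answer with useful precision.

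The documents do not support two stronger readings:
- **That recruitment stops once a wave is significant.** Three equally spaced looks at 0.05 would give 10.7%. The protocol speaks of setting a number to invite and states no stopping for significance, so that figure does not describe this design.
- **That the preliminary analyses breach concealment.** The Randomisation section says that "the research team will not know which group each participant is assigned to until after outcomes are assessed". Analysing a wave whose outcomes are complete is consistent with this. Allocation is by computer, recruitment by mass e-mail and outcomes by web survey, so knowledge of wave 1 results has no evident route to later allocation or measurement.

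**Conclusion.** The concern holds at moderate size and should be fixed. It does not invalidate the trial. On the reading closest to the text, type I error per test is about 5.6% to 6.7%, and a true 5.5% reduction is estimated on average as 5.7% to 6.0%. If recruitment could end after the first university, the figures are about 6.5% to 7.5% and 6.2% to 6.5%.

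These figures assume that wave 1 yields a third of planned N, that sizes are reset to 80% power at the observed effect, and that all waves are pooled without adjustment. They concern one hypothesis and one outcome. The exaggeration applies when there is a true effect; under the null the mean estimate is zero.

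The imprecision of wave 1 does not depend on the resizing rule. Between the 10th and 90th percentiles of its estimate, the implied sample size varies about 75-fold (45,100 / 610 ≈ 74), so it is a poor guide to later recruitment under any rule.

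**What to change.** Amend the Setting and Sample size estimation sections so that:
1. The target difference stays at the stated 5.5%. If the team considers another value more relevant, it should choose and justify it before any wave is analysed by group.
2. After each wave, later invitations are set only from pooled, arm-blind quantities: outcome mean, dispersion, response rate, proportion eligible on AUDIT-C and follow-up rate.
3. No between-group estimate is computed until the last wave has been followed up.

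This takes about two sentences and no change to randomisation or outcomes. It removes the effect-driven source of inflation and also addresses what is really uncertain in the calculation, namely the unstated mean and the dispersion, which the protocol already varies from 0.2 to 0.4. The cost is losing an early, imprecise look at the effect.

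If effect-driven resizing is kept, state the rule with its minimum and maximum, and combine waves by an inverse-normal test with weights fixed in advance. The 5.0% shown above is for two stages. If the third university may be dropped on the strength of the observed effect, that decision is a further interim look and must be covered by the prespecified method.
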